**Uveitis remission is defined as an inactive disease for 3 months after discontinuing all treatments for eye disease.**

- m. Vaccine inaccessibility, defined as proportion having gone to the vaccination site but refused due to the lack of vaccines, whereby this situation continues until the end of trial.
- n. Reasons for not yet vaccinated until the end of trial among those who should have been vaccinated per protocol.
- o. Change in anterior chamber cells from the Baseline to the end of three months.

- p. Change in vitreous haze from the Baseline to the end of three months.
- q. Change in best corrected visual acuity LogMAR score from the Baseline to the end of three months.

#### **6.4 Systemic Outcomes**

The systemic outcome will be systemic adverse events (apart from uveitis related events).

#### **6.5 Pre-specified Subgroup Analyses**

To determine differences between assignment groups in outcomes across subgroup variable defined by uveitis anatomical subtypes, etiology diagnosis classification, history of uveitis flare, age and sex.

## **7 Adverse Events**

### **7.1 Adverse Event Reporting**

An adverse event (AE) is defined as any unfavorable medical occurrence in a subject who has ever received study intervention, regardless of a causal relationship with this intervention. Any worsening of a pre-existing condition or illness should be considered an adverse event. Worsening in severity of a reported adverse event should also be reported as a new adverse event. An elective surgery/procedure scheduled to occur during a study will not be considered an adverse event if the surgery/procedure is being performed for a pre-existing condition and the surgery/procedure has been pre-planned prior to study entry. However, if the pre-existing condition deteriorates unexpectedly during the study (e.g., surgery performed earlier than planned), then, the deterioration of the condition for which the elective surgery/procedure is being done will be considered an adverse event. For adverse events to be considered intermittent, the events must be of similar nature and severity.

The Investigator will monitor each subject for clinical and laboratory evidence of adverse events throughout the study. The Investigator will assess and record any adverse event in detail including the date of onset, event diagnosis (if known) or sign/symptom, severity, time course, duration and outcome, relationship of the adverse event to study intervention and any actions taken. All these information on non-serious and serious adverse events will be recorded at each study visit.

### **7.2 Serious Adverse Events**

Serious adverse events (SAE) should be reported to Chief Investigator and Ethics Committee within 24 hours of the Investigator being made aware of the SAE. Serious adverse events include any medical occurrence that results in the following outcomes:

Death.

Life-threatening experience.

Non-elective surgery or hospitalization for any reason.

Congenital anomaly or birth defect.

Persistent or significant disability or incapacity.

Any other important medical events, not immediately life-threatening or resulting in death or hospitalization but requiring medical or surgical intervention to prevent serious outcome.

### **7.3 Severity Assessments**

The severity of adverse event can be assessed according to the following criteria:

Mild: The adverse event does not interfere with the volunteer's daily routine, and does not require intervention; it causes slight discomfort.

Moderate: The adverse event interferes with some aspects of the volunteer's routine, or requires intervention, but is not damaging to health; it causes moderate discomfort.

Severe: The adverse event results in alteration, discomfort or disability which is clearly damaging to health.

### **7.4 Causality Assessments**

The Investigator should assess the relationship of the adverse event with the use of vaccines by reporting according to the three-level classification of "associated", "not associated", and "inability to determine". Causality assessments will be required for study drugs as well as other adjunctive treatments.

### **7.5 Uveitis-Related Events**

The following events are known complications related to the condition being treated and will be classified as uveitis-related events. These events will be analyzed

separately from other adverse events in the final study report. Notably, the following events may not be a complete list of all potential uveitis-related events. The Investigators must determine if a specific event is uveitis-related.

Loss of transparency of the cornea.

Band keratopathy.

Synechiae.

Cataracts.

Glaucoma/increased intraocular pressure.

Vitreous hemorrhage.

Macular edema.

Retinal detachment.

Epiretinal membrane.

Vitreo-macular traction.

Retinal ischemia.

Vision loss.

Hypotony.

## **7.6 Pregnancy**

Subjects who become pregnant during the study period must be discontinued. Pregnancy in a study subject is not considered as an adverse event. However, the medical outcome of an elective or spontaneous abortion, stillbirth or congenital anomaly is considered as a serious adverse event.

## **7.7 Management**

For the purpose of medical management, all adverse events and laboratory abnormalities that occur during the study must be evaluated by the Investigator and treated according to the best medical judgment of their clinician. The occurrence of adverse events does not necessarily mean the time for the subject to exit the study. But, a serious adverse event will absolutely result in the discontinuation of the study immediately. For those developing non-serious adverse events, administration of other adjunctive treatments or even stopping the assigned intervention may be used.

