## **5.8    Withdrawn and Lost to Follow-up**

Subjects have the right to withdraw from the trial at any time and for any reason, without providing a reason. The investigator has the right to withdraw participants from the study and abandon assigned intervention strategies in the event of inter-current illness, adverse events, protocol violations or other reasons.

If the subject withdraws from the trial, efforts will be made to continue to obtain follow-up data, with the permission of the subject. They will be given appropriate treatment, but will not continue with scheduled study follow-ups unless they allow it.

Subjects will also be considered to have been withdrawn if they declare they are no longer interested in further participation, or have died. If the death is considered to be related to the vaccines, the subject will be declared serious adverse event, rather than withdrawn.

Missing a phone call or visit does not necessarily mean that a patient has been withdrawn from the study. For these subjects, efforts will be made to contact them and bring them back as soon as possible.

For those subjects fail to response the contact or to attend study visits without stating

an intention to withdraw from the study, the Investigator should contact the subject through telephone calls as soon as possible. The investigator will attempt to contact them for at least three times at each scheduled visit. If contact cannot be established up to the end of the trial, the subject should be considered as “lost to follow-up” on the date of last contact.

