### 6.3 Secondary Outcomes

- a. Time to clinically-confirmed uveitis worsening.

**Clinically-confirmed uveitis worsening is defined if any of the following criteria are met in at least one eye: new active, inflammatory chorioretinal or retinal vascular lesions (determined by clinical examination such as ophthalmoscopy or ancillary testing such as fundus photography and fluorescein angiography); worsening of best corrected visual acuity by 0.3 LogMAR score or more; a two-step increase in anterior chamber cell grade relative to baseline; or a two-step increase in vitreous haze grade relative to baseline. A 2-step increase is represented by a change of grade 0 to grade 2+; or grade 0.5+ to grade 3+.**

- b. Proportion of each reason for symptomatic uveitis worsening.
- c. Proportion of symptomatic uveitis worsening.
- d. Proportion of each reason for clinically-confirmed uveitis worsening.

- e. Time to initiation of step-up treatment.

**Step-up treatment is defined if any of the following criteria are met: addition of another systemic immunosuppressive agent (or biologics), switching to another systemic immunosuppressive agent (or biologics), or increasing doses of any currently systemically administered drugs.**

- f. Time to treatment interruptions.

**Treatment interruptions are defined if any of the following criteria are met: decreasing doses of or discontinuing any currently systemically administered drugs due to adverse events rather than disease improvement.**

- g. Time to hospitalization for any reasons.
- h. Time to hospitalization for ocular disease.
- i. Time to laboratory-confirmed COVID-19.
- j. Patient adherence, defined as proportion correctly vaccinated for at least one dose or maintaining not vaccinated per protocol throughout the trial.
- k. Proportion of vaccinated type and dose.
- l. Proportion of uveitis remission throughout the trial.

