## **10 Primary Outcome Comparison**

The primary outcome, time to uveitis symptomatic worsening over the course of 3 months of follow-up, will be compared with the Log-rank test. If a participant does not experience the primary endpoint event, they will have their data censored at the encounter where withdrawal or loss to follow-up occurs, or the final (month 3) follow-up encounter (whichever is earlier). For those with primary endpoint event, the censoring time point will be at the specific telephone call encounter (month 1, month 2, or month 3) where the occurrence of primary endpoint event is reported. Follow-up data after month 3 will no longer be included in the analysis, if any. The multiplicative limit method (Kaplan-Meier) will be used to show the cumulative incidence of primary endpoint event. A proportional hazard model (univariate Cox regression) is used to calculate the hazard ratio as well as 95% CI. The proportional-hazards assumption will be checked by means of inspection of a log-log survival plot.

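### Protocol 5.8, 7.6 and 7.7 can end outcome follow-up after a serious adverse event, a protocol violation or pregnancy, so censoring in the primary analysis may be informative

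*Supplement*

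**What the plan says.** Protocol 7.7 first says of adverse events in general: "The occurrence of adverse events does not necessarily mean the time for the subject to exit the study". It then makes an exception for serious ones: "But, a serious adverse event will absolutely result in the discontinuation of the study immediately". The list of serious events in protocol 7.2 includes "Non-elective surgery or hospitalization for any reason".

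Two further clauses can remove a patient. Protocol 5.8 allows the investigator to "withdraw participants from the study and abandon assigned intervention strategies in the event of inter-current illness, adverse events, protocol violations or other reasons". Protocol 7.6 discontinues subjects who become pregnant. On what follows withdrawal, 5.8 says that "efforts will be made to continue to obtain follow-up data, with the permission of the subject", but also that such patients "will not continue with scheduled study follow-ups unless they allow it".

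SAP 10 deals with participants who have not had the primary event: "they will have their data censored at the encounter where withdrawal or loss to follow-up occurs", or at month 3 if that comes first. SAP 8 has the same rule. SAP 13 plans 20 multiple imputations of primary-event status for those who withdraw or are lost, on the assumption that data are missing completely at random.

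Other sections expect observation to go on. SAP 7.1 keeps all randomized patients in the ITT population whatever their compliance. Protocol 5.6 keeps a deferred-arm patient who is vaccinated before remission under observation, and names hospitalization as one possible part of managing worsening. Protocol 6.3 has as separate outcomes time to any hospitalization and "Time to hospitalization for ocular disease", and changes in cells, haze and visual acuity at three months.

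**The concern.** The log-rank test and the Cox model need censoring that is unrelated to the outcome within each arm. Read together, these clauses can stop follow-up because a patient has been admitted, has had an adverse event or has departed from the assigned strategy. The first two are aspects of the health state being compared. The decision under 5.8 rests with the investigator, who knows the arm if he or she is also the treating ophthalmologist (protocol 5.3).

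If would-be events are cut off more often after prompt vaccination, the hazard ratio moves toward 1 and the prompt strategy looks safer than it is. Among the secondary outcomes, a first non-ocular admission can end the chance of seeing a later ocular one. Patients removed after an admission for uveitis can also be absent from the Month 3 visual comparison, which SAP 8 and 11.1 base on available data without imputation.

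**Working it through.** **1. What discontinuation means in 7.7**

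| Reading | Consequence | Support in the text |
|---|---|---|
| The subject leaves the study | Scheduled follow-up stops by default (5.8); censored under SAP 10 if event-free | The preceding sentence is about the subject's exit |
| The assigned strategy stops | Follow-up could continue | The following sentence speaks of stopping the intervention, but for non-serious events |
| The whole trial stops | One admission ends the trial | Literal wording only; hard to square with hospitalization as a compared outcome in 6.3 |

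The first reading fits best, but the text does not settle it.

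**2. What happens to data obtained after exit**

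Protocol 5.8 tries to obtain such data with permission. SAP 8 and 10 censor at withdrawal with no exception, so the data would not enter the primary analysis.

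**3. What SAP 13 repairs**

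The imputation uses baseline characteristics, assignment and completed encounters. The reason for leaving is not named as a predictor. MCAR is not credible for exits triggered by an SAE or adverse event.

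**4. How the plan's sample size treats dropout**

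Inputs (SAP 5): HR 1.5, 80% power, two-sided 0.05, event-free proportion 0.90 in the deferred arm, accrual in 3 of 6 periods, dropout 0.15. I assume that 0.90 applies at 3 periods. Freedman's formula needs 197 events. With follow-up of 3 to 6 periods the mean event probability is 0.178, so 197/0.178 = 1107, and 1107/0.85 = 1302. A Lakatos-type calculation gives 1094/0.85 = 1287. Both are within 3% of 1314. In this reconstruction, dropout is a plain inflation factor, unrelated to outcome.

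**5. Expected events in the analysis as specified**

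SAP 10 stops at month 3, so each patient contributes at most 3 months. Assuming exponential event times and dropout:

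- λ(deferred) = −ln 0.90/3 = 0.0351; λ(prompt) = 1.5 × 0.0351 = 0.0527; η = −ln 0.85/3 = 0.0542.
- P(event observed) = λ/(λ+η) × [1 − exp(−3(λ+η))].
- Deferred: 0.3933 × 0.2350 = 0.0924; × 657 = 60.7 events.
- Prompt: 0.4930 × 0.2743 = 0.1352; × 657 = 88.8 events.
- Total about 150 events.

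This is not the event count behind the 1314, which assumes longer follow-up (about 191 events by Schoenfeld's formula).

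**6. Illustration of lost events (all loss numbers assumed)**

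Losing k prompt-arm events only: HR ≈ 1.5 × (88.8 − k)/88.8. Power ≈ Φ(½√D × ln HR − 1.96), where D is the total number of events.

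| Assumed loss | D | HR | Power |
|---|---|---|---|
| None | 149.6 | 1.50 | 70% |
| 10% in both arms | 134.6 | 1.50 | 65% |
| 5 events, prompt only | 144.6 | 1.42 | 55% |
| 10 events, prompt only | 139.6 | 1.33 | 39% |

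Losses in the deferred arm only would push the other way: 1.5 × 60.7/(60.7 − k) gives 1.63 for k = 5 and 1.80 for k = 10. Starting instead from 191 events and 80% power, losing 5% or 10% of prompt-arm events gives HR 1.43 or 1.35 and power 67% or 52%; equal loss of 5% or 10% in both arms gives power 78.0% or 75.7%.

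**The case against.** A reader might infer three stronger things. The documents do not support them.

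- **That intention-to-treat is abandoned.** SAP 7.1 keeps every randomized patient and analyses them as randomized. Protocol 9.2 adds that the primary outcome must be available, but the SAP does not carry that condition. It is follow-up that is cut short.
- **That a patient admitted with a uveitis flare before the month 1 call is censored and so not counted.** The SAP 10 rule applies only to those without a primary event. Patients are told to phone at once with new symptoms (protocol 5.5), the symptom questions are also asked at unscheduled visits (5.7), and adjudicators see medical records as well as call records (SAP 3.1). Symptoms that meet the definition should count. SAP 10 leaves unclear how an event reported between scheduled calls is timed, which is a separate and smaller gap.
- **That the hazard ratios above estimate the bias.** They follow from assumed losses in one arm. The documents give no SAE or withdrawal rate.

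Other mitigation is real. Withdrawal under 5.8 is a right, not a duty. The most foreseeable violation, early vaccination in the deferred arm, already leads to continued observation under 5.6. Pregnancy is not shown to be related to ocular symptoms, so that censoring need not be informative. SAP 11.1 draws no inferences from secondary outcomes. Protocol 5.8 also classes a vaccine-related death as an SAE rather than a withdrawal, so the two are not plainly one category. If they differ, though, the SAP has no explicit rule for SAE discontinuation.

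What stands is that, on the natural reading of 7.7 and the plain text of 5.8, follow-up can end for health-related reasons, later data go unused in the primary analysis, and the planned sensitivity analysis assumes the problem away.

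**Conclusion.** The point holds as a risk of informative censoring created by clauses that conflict with each other. Protocol 5.8, 7.6 and 7.7 do not sit with protocol 5.6 and 6.3 or with SAP 7.1, and they must be reconciled. The conclusion rests on reading 7.7 as subject exit; the other readings need clarifying just as much.

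The size of the bias cannot be computed from the documents. It would be toward no difference if removals of would-be events were commoner in the prompt arm, and the hazard ratio would stay about the same if losses were proportional. Either way, events and Month 3 assessments can be lost that the existing schedule could have captured, and they may not be recoverable afterwards.

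**What to change.** In protocol 5.8, 7.6 and 7.7, separate stopping the assigned strategy from ending outcome follow-up, and say what discontinuation means in each place. State that outcomes continue to be collected through the scheduled calls and the Month 3 visit unless consent is withdrawn or contact is lost. Reconcile these sections with protocol 5.6 and 6.3 and SAP 7.1. Clinical handling after an SAE or a pregnancy remains with the investigators; this change concerns data collection only.

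In SAP 8 and 10, use data obtained after discontinuation, and censor only at consent withdrawal, last contact or month 3. In SAP 13, replace the MCAR assumption with missing at random, and add a delta-adjusted or tipping-point analysis for those who still leave.

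The cost is protocol and SAP wording, one further sensitivity analysis, and a few calls and visits that are already in the schedule.

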## **8 Data Collection and Management**

### **8.1 Confidentiality**

Participants will be identified via a unique ID. Identifiable information will not be stored in the eCRF and will not leave the site. Any participant contact information will be stored within the site on password protected computers or within secured locations with limited access. All study data and site files will be kept at site in a secure location with restricted access.

### **8.2 Source and Data Collection**

The study will employ an eCRF, whereby data will be managed via this system. Source data worksheets will be used for each patient and data will be entered onto the eCRF database. Source data worksheets will be reconciled at the end of the trial with the patients' medical notes in the study site. During the trial, critical clinical information will be written in the medical notes to ensure informed medical decisions can be made in the absence of the study team. Trial related clinical letters will be copied to the medical notes during the trial. The Chief Investigator will provide a signature for CRF once all queries are resolved and immediately prior to database lock.

It will be the responsibility of the Chief Investigator and his team to ensure the accuracy of all data entered in the worksheets and the eCRF are in accordance with Good Clinical Practice. The Principal Investigator will be responsible for ensuring that source data worksheets are filed in a suitably secure location to ensure source data verification can be undertaken throughout the study.

### **8.3 Quality Assurance**

The study will incorporate a range of data management quality assurance functions as the trial progresses. The Trial Data Manager will provide study training, ongoing

study support and will conduct regular monitoring, checking source data for transcription errors. Any necessary alterations to entered data will be date and time stamped within the eCRF. Regular monitoring of study conduct and data collected will be performed to ensure the study is conducted in accordance with GCP.

#### **8.4 Database Lock**

Prior to database lock, the Trial Manager will review any outstanding warnings on the eCRF and resolve or close these as appropriate before database lock. Local study personnel should resolve any queries that arise promptly. Once all queries have been resolved no further changes will be made to the database unless specifically requested by the Study Office in response to the Statistician's data checks. The study Chief Investigator will review all the data and provide electronic signature to verify that all the data are complete and correct. At this point, all data will be formally locked for analysis.

#### **8.5 Archiving**

Chief Investigator will be responsible for securely archiving local data generated, essential documents and source data in accordance with local requirements, but for at least 5 years from the end of the study.

## **9 Statistical Considerations**

### **9.1 Sample Size Calculation**

A two-sided log-rank test with an overall sample size of 1314 subjects (657 in the deferred vaccination group and 657 in the prompt vaccination group) achieves 80.0% power at a 0.050 significance level to detect a hazard ratio of 1.5 when the proportion surviving (no occurrence of symptomatic uveitis worsening) in the deferred vaccination group is 0.9000. The study lasts for 6 time periods of which subject accrual (entry) occurs in the first 3 time periods. The accrual pattern across time periods is uniform (all periods equal). The proportion dropping out of both groups is 0.1500, respectively.

### **9.2 Data Analyses**

Analysis methods of each study outcome will be provided in a detailed statistical analysis plan.

Primary analyses will be on an Intention-to-treat (ITT) basis. According to the intention-to-treat principle (ITT), all patients who have been randomized regardless of their compliance with the study intervention and whose primary outcome is available will be included, which is one of the main data sets for the effectiveness evaluation of this study. Given the pragmatic nature of the trial and the expected gaps in data on patient compliance with randomized intervention, we will not consider the per-protocol (PP) analysis as the primary analysis.

The clinical and demographic characteristics of the participants will be summarized with descriptive statistics. Continuous variables will be described with their distribution range, mean, median, standard deviation, and interquartile range, as appropriate. Categorical variables will be summarized as numbers and the proportions.

The primary outcome will be the time to symptomatic uveitis worsening. For the primary outcome, the multiplicative limit method (Kaplan-Meier) is used for univariate survival analysis, the median time to symptomatic uveitis worsening and survival rate of each group are calculated, and the survival rate curve is compared by the Log-rank test.

For the systemic outcomes, the types, number, and incidence of all systemic adverse events during the follow-up period will be described in a tabular form.

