q. Change in best corrected visual acuity LogMAR score from the Baseline to the end of three months.

r. Incidence of any systemic adverse event (apart from uveitis related events).

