LogMAR, light perception (LP) as 2.3 LogMAR, and no light perception (NLP) as 3.0 LogMAR. Otherwise, numerical visual acuities will be transformed with the formula:  $\log\text{MAR} = -\log_{10}(\text{visual acuity fraction})$ .

- r. Incidence of any systemic adverse event (apart from uveitis related events).

Descriptive analysis will be used to report the incidence of any systemic adverse event.

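### The systemic safety summary pools all events and leaves out the recorded severity and seriousness, so a difference in severe or serious events can be masked or reversed

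*Supplement*

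**What the plan says.** The stated safety objective (protocol 2.4, SAP 2.3) is to evaluate systemic adverse events under the two strategies. Protocol 9.2 leaves methods to the SAP but says of systemic outcomes that "the types, number, and incidence of all systemic adverse events during the follow-up period will be described in a tabular form". SAP 3.2 r lists one safety outcome, the incidence of any systemic event other than uveitis-related ones, and 11.2 r gives its method: "Descriptive analysis will be used to report the incidence of any systemic adverse event".

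The protocol collects more than this. Section 7.1 has each event recorded with its "severity, time course, duration and outcome, relationship of the adverse event to study intervention and any actions taken". Section 7.3 supplies a mild, moderate and severe scale, introduced by "The severity of adverse event can be assessed according to the following criteria". Section 7.2 defines seriousness: "Serious adverse events include any medical occurrence that results in the following outcomes", with a list that includes death, life-threatening experience, hospitalization and disability. Section 7.1 also sets a reporting rule: "Worsening in severity of a reported adverse event should also be reported as a new adverse event".

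Neither 9.2 nor SAP 11.2 r splits systemic events by severity or seriousness.

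**The concern.** The prompt arm is advised to be vaccinated as soon as possible, and unvaccinated participants are encouraged again at each call (protocol 5.5, 5.6). The deferred arm is advised to wait for remission, which requires three months of inactive disease off all eye treatment. Patients already in remission are excluded (4.2) and follow-up lasts three months (3.1). During the analysed period the arms are therefore meant to differ in vaccination.

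Every participant is also asked monthly about other ocular or systemic symptoms (Question 7 in both modules). If vaccination brings frequent mild reactions, the any-event figure will largely reflect them. The clinically weightier question is whether severe or serious systemic events differ between strategies, and the safety summary has no row that answers it.

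**Working it through.** **No plan figure to reproduce.** The documents give no adverse event rates and no precision target for safety. The only input taken from them is the arm size, 657 (protocol 9.1, SAP 5). All rates below are assumptions, and differences are prompt minus deferred.

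**Step 1: precision of the any-event row.** Half-width = 1.96 × √[p₁(1−p₁)/657 + p₂(1−p₂)/657]. Assume 5% with any systemic event in the deferred arm and 15% to 40% in the prompt arm.

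- 15% versus 5%: 1.96 × √[(0.1275 + 0.0475)/657] = 3.2 points around a difference of 10.
- 25% versus 5%: 1.96 × √[(0.1875 + 0.0475)/657] = 3.7 points around 20.
- 40% versus 5%: 1.96 × √[(0.2400 + 0.0475)/657] = 4.1 points around 35.

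A doubling of severe or serious events from 1% to 2% (0.01 × 657 = 6.6 and 0.02 × 657 = 13.1 participants) moves the any-event incidence by at most 1 point, well inside each half-width.

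**Step 2: can the pooled row point the wrong way?** Treat mild and serious events as independent, so any = 1 − (1 − mild)(1 − serious). Intervals for differences are 95% Newcombe intervals built from the Wilson limits of each arm. Example for the second row of the table: prompt 1 − 0.95 × 0.995 = 5.48%; deferred 1 − 0.99 × 0.98 = 2.98%; difference +2.50.

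| Mild, prompt / deferred | Serious, prompt / deferred | Serious row, points (95% CI) | Any-event row, points (95% CI) |
|---|---|---|---|
| 0% / 0% | 0.5% / 2.0% | −1.50 (−2.92 to −0.28) | −1.50 (−2.92 to −0.28) |
| 5% / 1% | 0.5% / 2.0% | −1.50 (−2.92 to −0.28) | +2.50 (0.31 to 4.77) |
| 10% / 2% | 0.5% / 2.0% | −1.50 (−2.92 to −0.28) | +6.49 (3.73 to 9.35) |
| 30% / 5% | 0.5% / 2.0% | −1.50 (−2.92 to −0.28) | +23.45 (19.41 to 27.45) |
| 30% / 30% | 2.0% / 0.5% | +1.50 (0.28 to 2.92) | +1.05 (−3.94 to 6.03) |

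Without mild reactions the two rows agree. With unequal mild rates the sign reverses. With equal but common mild reactions the difference is blurred.

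**Step 3: what other outcomes cover.** Time to hospitalization for any reason (outcome g) captures one criterion of seriousness, but mixes systemic with ocular admissions. Outcome h covers ocular admissions only. Outcome f captures dose reduction or stopping of systemic drugs because of adverse events. No by-arm row remains for deaths, for life-threatening or disabling events without admission, or for severe non-serious events. Deaths need explicit mention: 7.2 lists death as a serious outcome, while 5.8 treats deaths not considered vaccine-related as withdrawals.

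**Step 4: the event number.** Under 7.1, an episode recorded first as mild, then moderate, then severe would yield three reports. Neither document says how reports are collapsed, or whether the unit is the participant or the event. The number in 9.2 can therefore exceed the number of episodes. A per-participant incidence cannot be inflated this way.

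**The case against.** The case on the other side has substance.

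- Protocol 9.2 tabulates types of event, so different kinds would be listed apart. This stands. What is lost is severity and seriousness within a type.
- Outcomes f and g carry some of the serious consequences, and individual cases are escalated: "Serious adverse events (SAE) should be reported to Chief Investigator and Ethics Committee within 24 hours". It would be wrong to infer that seriousness goes unexamined. Expedited reporting is not a comparison by arm, however, and the gaps in Step 3 remain.
- The 7.1 sentence is a reporting rule, the SAP plans only an incidence, and contacts are mainly monthly. A brief reaction may be reported once, after the fact. A reader might infer that every worsening reaction is counted several times in the analysis; the documents show only that this can happen to the number in 9.2.
- A reader might also infer that mild reactions are bound to swamp any serious difference. With no rates in the documents, that is a prediction, not a finding.
- A separate row would not settle the matter either. At 2% versus 1% its half-width is 1.96 × √[(0.0196 + 0.0099)/657] = 1.3 points, so 1.0 ± 1.3 runs from −0.3 to 2.3 and includes zero. This stands in full.
- SAP 11.1 draws no inference from secondary outcomes, and the data are collected in any case, so the rows could be added at reporting. That is true, but choosing safety rows in advance is better than choosing them once the results are known.

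**Conclusion.** The concern holds in a limited form. The planned systemic safety summary does not use the recorded severity or seriousness, and the difference in vaccination between arms makes the pooled figure a poor guide to severe or serious events. Pooling can mask or reverse such a difference: in the illustration, −1.5 points becomes anything from +2.5 to +23.5, depending on the assumed mild rates. The sizes rest on those assumed rates, on independence of mild and serious events, and on 657 analysed per arm.

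The documents do not support saying that a serious difference is certain to be hidden. The primary comparison is not affected, and no data are lost. The point concerns how well the plan answers its own safety objective.

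**What to change.** In SAP 11.2 r and protocol 9.2, keep the any-event row and add two rows by arm: participants with at least one severe systemic event (7.3 grading), and participants with at least one serious systemic event (7.2 definition), stating that all deaths are included. Classify each participant once, by worst grade. Give the difference with the Wilson-based interval already planned for the other proportions. State that incidences are per participant. Where event numbers are shown, count each episode once at its worst severity.

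The cost is a few lines of SAP wording and two table rows from data the protocol already requires. Intervals for rare events will be wide, so the rows should be labelled descriptive; their value is in showing the counts by arm.
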